##### Monitoring and Ongoing Feedback of User State

Specific practices related to the therapeutic activities or skills that are currently being taught are documented within the system using a brief daily report that includes no more than 7 logic-driven multiple-choice questions and takes less than 2 minutes to complete. These questions ask about parental practices based on a step-by-step script. This is meant to help the parent implement the new way of thinking during their interactions with their child. The program offers nonjudgmental feedback, recognizes desirable achievements based on operant theory, and sends specific messages related to the parent’s current report to help increase motivation for change or reveal new information. For example, across disciplines, positive feedback following positive behavior improves outcomes, whereas negative feedback following failure may reduce motivation and efficacy [61-63].

##### Adaptation to User State

At the end of the first module (introduction), parents will be asked to report about the current state at home, and this will be used to recommend whether to complete the 3 learning modules that are not deemed obligatory: positive interactions, emotion regulation, and effective routines. Parents’ reports on their activities are used to acknowledge their success and to suggest additional actions based on the specific goals reported by parents. Effort related to desired therapeutic activities is adapted based on graded tasks (defined as “load reduction of therapeutic activities” in our therapeutic persuasiveness model [13]). For example, when parents learn how to overcome disobedience (module 6), they will be guided to choose 1 specific behavior problem they would like to focus on first, and then, based on their progress, they will be directed to take additional steps.

#### Therapeutic Persuasiveness Fidelity

Our approach integrates elements such as clear goal relevance, continuous monitoring and feedback, and adaptation to the user’s state. To achieve a satisfying user experience, it is essential that these elements work together effectively. When the users are explicitly required to achieve goals, their goal achievements are expected to be monitored, and it would make sense to also provide them with feedback, and so on. For this reason, the individual components of TP are interrelated and not distinguished in our manipulation. However, using the Enlight quality expert rating scale [13], we evaluated both programs. The DPT-STD design received a TP score of 2.1, which is near the “poor” category, whereas DPT-TP earned a 4.5, placing it between “good” and “very good” scores [39].

### Analytic Plan

#### Preprocessing Steps: Data Audit and Missing Data

The final trial dataset will be accessed by the research coordinators, a statistician, and the principal investigator. Preprocessing will include an examination of data accuracy to identify and correct errors and to ensure that all data are in range. In addition, univariate outliers will be identified (observations that are 3 SDs from the mean in both directions) and will be corrected using winsorizing [64]. Normality (ie, skewness and kurtosis) will be examined for all variables using standard tests (Shapiro-Wilk test and Kolmogorov-Smirnov test). If data significantly differ from a normal distribution according to these tests, we will use transformations depending on the precise deviations from normality (eg, positive skewness, negative kurtosis). Possible transformations will include square root, natural log, inverse, and the Box-Cox transformation [65]. The pattern of missing data will be assessed using Little’s Missing Completely at Random test. Data that are missing completely at random or missing at random will be imputed using multiple imputations with 5 datasets. All preprocessing will be done using SPSS software (IBM Corp).

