#### Recruitment Procedure

Parents will be recruited through relevant social media parenting groups, Facebook advertisements, and pamphlets sent to relevant childcare settings. Prospective participants will be directed to the project website, which will offer basic information and a link to a brief eligibility screener consisting of the exclusion criteria and 9 items assessing the parents’ experience of their child’s behavior, based on *Diagnostic and Statistical Manual of Mental Disorders, Fifth Edition* criteria for oppositional defiant disorder (to pass screening parents had to receive an average of 4.22 or above). Screening, interest, and parents’ understanding of the terms of the study will be confirmed by a phone call with a research assistant. Parents will then be directed to a web-based informed consent form, followed by the baseline assessment battery. Once participants have completed baseline assessments and are deemed eligible, they will be randomly assigned to one of the 2 conditions (1:1), stratified for child gender, by an independent researcher who is blind to their assessments and has exclusive access to the assignment sequence. A computer-generated randomization procedure will be used with randomly generated block sizes of 2, 4, and 6. Ineligible participants will be informed about available public mental health care services.

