#### Power Estimation

Data emerging from the pilot suggest a large effect size difference in module completion rates and medium effect size differences between the 2 intervention groups in terms of change in ECBI scores and parenting variables post intervention (eg, primary hypothesis Cohen *d*s=0.43; 0.54) [39]. Taking the smaller effect size as an approximation (Cohen *d*=0.43), a total sample size of 80 participants in each of the 2 conditions and a total of 160 participants will provide 0.85 power (α=.05, 1-tailed) to detect significant differences in the primary outcomes (intent-to-treat analysis).

For our mediation analyses, we assume a large effect size difference in program completion rate based on TP quality (the A path), and a small to moderate effect size (correlation) between program completion and change in child behavior problems (the B path). Therefore, a sample size of 160 participants in total is higher than 150 participants, which would be sufficient to examine the relationship between program completion rate (the mediating variable) and child behavior problems (the predicted variable; for a review of sample size estimations for mediation effects, see [69]).

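### Imputation is conditioned on a missing-data mechanism that cannot be verified, and five datasets leave p values near 0.05 dependent on the random seed

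*Protocol article*

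**What the plan says.** Under Preprocessing Steps: Data Audit and Missing Data, the protocol article names one diagnostic: "The pattern of missing data will be assessed using Little’s Missing Completely at Random test". The next sentence gives the rule: "Data that are missing completely at random or missing at random will be imputed using multiple imputations with 5 datasets". No other means of recognising MAR data is named, and nothing is said about data judged to be neither MCAR nor MAR.

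Under Power Estimation, the article plans "a total sample size of 80 participants in each of the 2 conditions and a total of 160 participants", which "will provide 0.85 power (α=.05, 1-tailed) to detect significant differences in the primary outcomes (intent-to-treat analysis"). It states no expected rate of missing assessments and adds no allowance for them.

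Under Hypotheses 1-2 Analytic Plan, efficacy is tested by two-way ANOVAs of pre against post and pre against follow-up, so each family needs a value at both time points, observed or imputed.

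**The concern.** The rule has two weak parts.

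- **The condition.** Imputation is authorised only for data with a given missingness mechanism, but the one diagnostic named cannot establish that mechanism. If the team judged the data to be neither MCAR nor MAR, the text would not say how families without a T4 or T5 score enter an analysis described as intent-to-treat. That decision would then be made after the data are seen.
- **The number of datasets.** Five is a fixed choice. With so few, the pooled estimate carries visible simulation noise. Two analysts running the same plan on the same data with different seeds could report different p values, and near 0.05 they could reach different verdicts on the efficacy hypothesis.

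**Working it through.** **The plan's own figure.** Inputs from Power Estimation: 80 per arm, d = 0.43, alpha 0.05 one-tailed. The noncentrality is 0.43 × √(80/2) = 2.72. Power is Φ(2.72 − 1.645) = 0.859 by the normal approximation and 0.856 by the noncentral t with 158 df. The stated 0.85 reproduces, with every family contributing an outcome.

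**The condition, case by case.**

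1. Little's test does not reject. This does not establish MCAR; it fails to find evidence against it.
2. Little's test rejects. The data are then taken as not MCAR. MAR and MNAR differ in how missingness depends on the unseen values, so observed data cannot choose between them.
3. The data are judged neither MCAR nor MAR, on whatever grounds. The rule has no instruction.

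So the condition cannot be checked in cases 1 and 2, and the plan is silent in case 3.

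**Five datasets: precision.** With m the number of imputations, relative efficiency is 1/(1 + FMI/m). The documents give no missing rate, so FMI is assumed over a range.

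**Five datasets: reproducibility.** The pooled estimate varies over seeds with variance B/m, where B is the between-imputation variance. Since B is about FMI × SE², the Monte Carlo SD is about √(FMI/m) standard errors. The last two columns take a result whose t would be 2.0 with unlimited imputations, use 2.0 ± 1.96 × Monte Carlo SD, and convert to two-sided normal p values.

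| Assumed FMI | Relative efficiency, m = 5 | Monte Carlo SD, m = 5 (SE) | Monte Carlo SD, m = 50 (SE) | p range over seeds, m = 5 | p range over seeds, m = 50 |
|---|---|---|---|---|---|
| 0.1 | 0.98 | 0.14 | 0.04 | 0.023 to 0.085 | 0.037 to 0.056 |
| 0.2 | 0.96 | 0.20 | 0.06 | 0.017 to 0.108 | 0.034 to 0.061 |
| 0.3 | 0.94 | 0.24 | 0.08 | 0.013 to 0.129 | 0.031 to 0.065 |
| 0.4 | 0.93 | 0.28 | 0.09 | 0.011 to 0.148 | 0.030 to 0.068 |

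Example for FMI 0.2, m = 5: √(0.2/5) = 0.20, and 2.0 ± 1.96 × 0.20 gives t from 1.61 to 2.39. With m = 50, relative efficiency is at least 0.99 throughout.

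**Simulation check.** Forty trial datasets were generated with 80 per arm, a change-score effect of 0.43 SD, an assumed pre-post correlation of 0.5 and T4 missing completely at random. Each was imputed with 60 seeds, pooled by Rubin's rules and tested two-sided at 0.05. The share of datasets in which more than 5% of seeds gave the minority significance verdict was:

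| Assumed missing at T4 | m = 5 | m = 50 |
|---|---|---|
| 10% | 18% | 5% |
| 20% | 28% | 15% |
| 30% | 43% | 15% |
| 40% | 50% | 5% |

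At 30% missing, in the dataset with median p nearest 0.04, the 5th to 95th percentile range of p over seeds was 0.014 to 0.112 with m = 5 (median 0.045) and 0.033 to 0.056 with m = 50 (median 0.040). With only 40 datasets these shares are noisy, as the uneven m = 50 column shows. They support the direction and rough size of the formula, no more.

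**The case against.** **The rule can be run as written.** If Little's test cannot return a finding of MNAR, a natural reading is that non-rejection is treated as MCAR and rejection as MAR, and both lead to imputation. The article says that the test assesses the pattern; it does not say that the test decides whether to impute. This stands against any claim that the rule cannot be executed. It does not repair the text, which still limits imputation to mechanisms nobody can confirm and has no branch for other data.

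**Five imputations are a matter of degree.** Every finite number leaves some seed dependence, efficiency is hardly affected, and the size depends on missing rates that the article does not give. All of this stands. The effect is modest at 10% missing and matters only for results near the threshold. The choice of about 50 is a practical one, not a sharp limit.

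**Stronger readings that the documents do not support.**

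- A reader might infer that the analysis falls back to completers. Power would then be 0.825, 0.785, 0.736 and 0.678 at 10%, 20%, 30% and 40% missing. The article nowhere says this and labels the analysis intent-to-treat.
- A reader might infer arm-dependent questionnaire dropout from the pilot's 68.9% against 27.9%. Those figures are program completion, not assessment response, and under Ethics Approval families are paid for assessments whatever their program use. MAR imputation with arm in the model also handles dropout that merely differs by arm.
- A reader might infer that differential dropout and MNAR data will go unexamined. Dropout comparisons and sensitivity analyses are commonly left to the full protocol or analysis plan, which are not shown, so the article's silence is not an error.

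**Conclusion.** The concern holds for two things that the article itself fixes. Imputation is conditioned on a mechanism that Little's test cannot establish, with no handling for data judged otherwise, and the intent-to-treat analysis is undefined in that case. This part rests on logic and needs no assumed figure.

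Setting five datasets costs 2% to 7% in relative efficiency but leaves a Monte Carlo SD of about 0.14 to 0.28 standard errors, roughly three times that with 50 datasets (√(50/5) = 3.2). The size rests on an assumed FMI of 0.1 to 0.4 and bears on the verdict only when the result lies near 0.05. The p ranges are two-sided; a one-tailed test would move the threshold, not the spread of the estimate.

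The documents do not show that dropout will differ by arm, that completers will be analysed, or that bias will follow. The point is worth correcting before analysis, which Table 1 schedules to begin in January 2027.

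**What to change.** Replace the rule in the missing-data section as follows:

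- Drop Little's test as a condition for imputing. It may stay as a description.
- State MAR as the working assumption of the primary analysis, and impute for all randomised families.
- Include arm, the outcomes at the other time points, child gender (the stratification factor) and the automatically logged program usage in the imputation model.
- Use about 50 datasets with a seed fixed in advance.

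The planned ANOVAs need not be replaced. A delta-adjusted sensitivity analysis for T4 ECBI by arm would be a useful optional addition.

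The cost is plan wording and computing time. No new data are needed, and the sample size and assessments do not change.

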#### Hypotheses 1-2 Analytic Plan

Hypothesis 1 will be examined using a series of 1-way ANOVAs. Specifically, treatment type will be the independent variable (DPT-STD vs DPT-TP) in all analyses, and program completion rate, number of logins, unique days of use, and total time of use will be the dependent variables. If the treatment conditions significantly differ on important demographic or clinical variables, those variables will be added as covariates to the analysis, creating an analysis of covariance (ANCOVA).

Hypothesis 2 will be examined using two 2-way ANOVAs with treatment type (DPT-STD vs DPT-TP), measurement (pre vs post in the first ANOVA and pre vs follow-up in the second), and their interaction as independent variables. Child behavior problems (ECBI Intensity), parenting practices (SPP, PS scales, and APQ), and parental self-efficacy (PTC and MaaP) will be the dependent variables.

Assumptions of ANOVA will be examined for all analyses and corrected if not met using common procedures. For instance, the assumption of equality of variance will be examined using the Levene test, and if not met, we will use weighted least squares or robust tests such as Welch and Brown-Forsythe.

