#### Mediation Analyses (Hypothesis 3 and Exploratory Examination)

These analyses will be based on the criteria of Zhang et al [66] for mediation in multilevel models. A 2-1-1 mediation model (Figure 2) in which the predictor (TP quality) is a level-2 antecedent variable (between-subjects variable) will be used. The potential mediator (program completion rate) and outcomes (child behaviors and parenting variables) are both level-1 variables (ie, repeated measurements-within-subjects variables). This model tests whether the study manipulation of predictor values influences the values of a level-1 mediator, which then affects a level-1 outcome. Mediation analyses will be conducted using relevant codes for Mplus (Muthén and Muthén) [67,68].

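### Hypothesis 1 adds covariates only where baseline differences are significant, and the stratification factor, child gender, is in no described model

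*Protocol article*

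**What the plan says.** The protocol article, under Hypotheses 1-2 Analytic Plan, sets out the usage and completion analysis as follows: "Hypothesis 1 will be examined using a series of 1-way ANOVAs", and "treatment type will be the independent variable (DPT-STD vs DPT-TP) in all analyses". The same paragraph gives the covariate rule: "If the treatment conditions significantly differ on important demographic or clinical variables, those variables will be added as covariates to the analysis". It does not list the candidate variables, name the baseline test or state its level.

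Under Recruitment Procedure, families are "randomly assigned to one of the 2 conditions (1:1), stratified for child gender", with "randomly generated block sizes of 2, 4, and 6".

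The efficacy analysis (Hypothesis 2) is given as "two 2-way ANOVAs with treatment type (DPT-STD vs DPT-TP), measurement (pre vs post in the first ANOVA and pre vs follow-up in the second") plus their interaction. That paragraph has no covariate rule and no gender term. The mediation section names trial arm as the level-2 predictor and does not mention gender.

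**The concern.** In a properly randomised trial, a baseline difference between arms is a chance event whatever its p-value. Whether a covariate is worth including depends on how strongly it predicts the outcome, and the rule does not ask that. A strongly prognostic variable that happens to be balanced stays out, and an irrelevant one that happens to be imbalanced goes in. The model to be reported is known only after the baseline data have been tested. Because the candidate variables are not named, the analyst also has room to decide which ones count.

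The rule also works against the design. Gender is balanced by stratified blocks, so an imbalance test will hardly ever select it. Whatever outcome variance gender explains then stays in the error term, although the design has already removed its contribution to the difference between arms. The standard error is overstated to that extent.

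At stake are precision, correct calibration of the test and a model fixed in advance.

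**Working it through.** **1. The plan's own figure.** Inputs from Power Estimation: 80 per arm, d=0.43, α=.05 one-tailed, power 0.85. The noncentrality is 0.43 × √(80/2) = 2.720. Power = Φ(2.720 − 1.645) = 0.859 (0.856 with the t distribution). The stated 0.85 reproduces for an unadjusted comparison.

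**2. How often the rule changes the model.** For k independent baseline tests at .05, the chance of at least one significant result is 1 − 0.95^k. The article gives neither k nor the level, so both are assumptions.
- k=5: 0.23
- k=8: 0.34
- k=10: 0.40

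**3. Whether gender could trigger it.** With blocks of at most 6, an unfinished last block leaves an imbalance of at most 3 per stratum. Assume a near-even split of 81 boys and 79 girls. The worst case is then 42 boys of 80 against 39 of 80. z = (0.5250 − 0.4875)/√(0.25 × 2/80) = 0.0375/0.0791 = 0.47, far below 1.96. Missing data could disturb this, hence almost never rather than never.

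**4. Cost of leaving gender out.** Let gender explain a share R² of outcome variance (not given in the article; assumed 1% to 20%). With gender balanced by design, the true standard error is smaller than the unadjusted one by √(1 − R²). Put f = 1/√(1 − R²). For a single-outcome comparison, one-sided .05:
- type I error, unadjusted: 1 − Φ(1.645f)
- power, unadjusted: Φ((2.720 − 1.645)f)
- power, gender in the model: Φ(2.720f − 1.645)

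| Gender R² | Type I, unadjusted | Power, unadjusted | Power, with gender | Points lost |
|---|---|---|---|---|
| 1% | 0.049 | 0.860 | 0.862 | 0.2 |
| 5% | 0.046 | 0.865 | 0.874 | 0.9 |
| 10% | 0.042 | 0.871 | 0.889 | 1.8 |
| 20% | 0.033 | 0.885 | 0.919 | 3.3 |

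The table follows the one-tailed convention of the power statement. For a two-sided .05 test, type I error runs from 0.049 to 0.028 and the loss from 0.3 to 5.8 points over the same R² range.

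**5. The selection rule itself.** This was simulated with 160 families, gender-stratified blocks of 2, 4 and 6, five baseline covariates tested at .05, and 4,000 runs per setting. One-sided type I error under the rule was 0.038 to 0.047. With gender R² 5% and one covariate of R² 25% (both assumed), power at d=0.43 was:
- 0.862 unadjusted
- 0.867 under the rule
- 0.871 with gender alone
- 0.944 with gender plus the prespecified covariate

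The last figure shows what a strong covariate can give. Nothing in the article shows that baseline ECBI predicts usage that well.

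**The case against.** The strongest reply is that little hangs on this where the rule applies. The pilot's usage effects were d=0.91 to 2.22, and completion was 68.9% against 27.9%. At d=0.91 with 80 per arm, two-sided power is Φ(0.91 × √40 − 1.960) = Φ(3.80), above 0.999. A covariate more or less is unlikely to change a Hypothesis 1 conclusion. This stands, and it limits the size of the point.

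A second reply is that an article may leave covariates to a fuller document. That is fair for its silence on covariates in Hypotheses 2 and 3. It does not cover Hypothesis 1, where a test-driven rule is stated outright.

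A reader might infer more than the article supports:
- **That the whole analysis is data-driven.** The rule stands in the Hypothesis 1 paragraph only. The Hypothesis 2 terms are fixed as written.
- **That baseline ECBI goes unused for efficacy.** It enters the Hypothesis 2 ANOVA as the pre measurement, and the interaction compares change from it.
- **That omitting the stratum inflates false positives.** The calculation shows the reverse: the test is conservative.
- **That gender matters equally for Hypothesis 2.** A stable gender difference in level cancels in the pre-post contrast; only a relation to change helps.

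**Conclusion.** The point holds for Hypothesis 1 as a poor method that the article states. The rule selects covariates on the wrong criterion and leaves the model open until the data are seen. The trigger rates of 23% and 40% show how often the model would change, not how often a conclusion would.

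The effect of omitting gender is small and in the conservative direction. At a gender R² of 1% to 5% the loss is under one point of power at d=0.43, and the 3.3-point loss needs an R² of 20%. These sizes rest on the assumed R² and on an effect of d=0.43, which is the ECBI planning value and not a usage effect. The stated 0.85 power needs no correction on this account. The change is worth making because it is cheap and removes avoidable discretion, not because validity is threatened.

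**What to change.** - Delete the significance-triggered sentence. Name child gender and baseline ECBI Intensity as covariates in every Hypothesis 1 model, whatever balance is observed.
- Include child gender in the Hypothesis 2 models, with its interaction with measurement, since a gender main effect alone drops out of the pre-post contrast.
- Do not add baseline ECBI to the pre/post ANOVA for ECBI, where it is already the pre level. Adjusting for an outcome's own baseline there would mean replacing that ANOVA with ANCOVA, which is a separate change.

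The downside is small. No new data are needed: gender is known at randomisation and ECBI is collected at T1. The study is preregistered and 100 families were enrolled by the end of December 2024, so the change needs a documented amendment before analysis begins, scheduled for January 2027.

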**Objective:**

This study aims to (1) examine the impact of TP quality on usage, reduction in child behavior problems, and improvement in parenting variables; (2) examine the maintenance of treatment gains over a follow-up period; and (3) examine mediational pathways, including whether adherence to the program (measured by module completion rates) mediates reported changes.

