### This Study

This study aims to (1) conduct a fully powered RCT design that can provide strong support for the hypotheses; (2) examine the long-term impact of the treatment and the maintenance of treatment gains over a follow-up period, knowledge that is of great importance when aiming to determine whether enhanced mechanisms of action embedded in unguided interventions are maintained over time (or even better in comparison with standard programs); and (3) examine meditational pathways including whether adherence to the program, measured by module completion rates, mediate reported changes.

The study design is a 2-arm parallel-group RCT with repeated measures. It consists of 2 intervention arms for parents of children with behavior problems. We will follow a large sample of families with parents who report having a child with behavior problems, before, during, and after receiving the DPT they are randomly allocated. In particular, this study has the following hypotheses:

Adherence and usage: Compared with parents who receive DPT-STD, parents who receive DPT-TP will show better adherence to the digital program (operationally defined as program completion rate) and higher metrics of program usage (number of logins, unique days of use, and total time of use).Efficacy: Compared with parents who receive DPT-STD, parents who receive DPT-TP will report greater improvements in child behavior problems (Eyberg Child Behavior Inventory [ECBI] Intensity), parenting practices (Specific Parenting Practices [SPP], The Parenting Scale [PS], and Alabama Parenting Questionnaire [APQ]) and Parental self-efficacy (The Parenting Tasks Checklist; Me as a Parent [MaaP]), as measured pre-post and pre-follow-up.Mediational pathway: Program completion rate will mediate the impact of therapeutic persuasiveness quality on outcome variables.

In addition, we will explore whether the relationship between program usage and changes in parenting variables and child behavior problems is moderated by program quality (moderated mediation).

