### Measures

The study instruments include self-reported questionnaires that will be assessed at all time points for this study (T1-T5) and data on program usage. Parents will also complete a demographic questionnaire at baseline (T1). Participants will be assessed at 3.3 weeks (T2), 6.6 weeks (T3), and 10 weeks (postintervention; T4), and will complete follow-up assessments at 6 months after the beginning of the intervention (follow-up; T5). The self-report measures will be administered through Qualtrics (Silver Lake).

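### The Hypothesis 2 pre/post ANOVAs are valid and meet the stated power, but they are less efficient than adjusting for the baseline score, and no T4-to-T5 contrast addresses maintenance of gains

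*Protocol article*

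**What the plan says.** Under Hypotheses 1-2 Analytic Plan, the article states: "Hypothesis 2 will be examined using two 2-way ANOVAs with treatment type (DPT-STD vs DPT-TP), measurement", the latter being "pre vs post in the first ANOVA and pre vs follow-up in the second), and their interaction as independent variables". The baseline score is therefore one level of the time factor and is not a covariate. The only covariate rule in that section stands in the Hypothesis 1 paragraph and is conditional: "If the treatment conditions significantly differ on important demographic or clinical variables, those variables will be added as covariates to the analysis".

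This matches the wording of Hypothesis 2 (This Study), which expects greater improvement "as measured pre-post and pre-follow-up".

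The Measures section schedules two further waves during treatment: "Participants will be assessed at 3.3 weeks (T2), 6.6 weeks (T3), and 10 weeks (postintervention; T4"), with T5 at six months after the start of the intervention. Those waves do not enter the Hypothesis 2 tests. In the mediation section, however, the mediator and the outcomes "are both level-1 variables (ie, repeated measurements-within-subjects variables").

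Aim 2 (This Study) is to "examine the long-term impact of the treatment and the maintenance of treatment gains over a follow-up period"; the abstract's Objective says the same of maintenance.

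**The concern.** With two waves and two arms, the arm-by-measurement interaction is identical to a two-sample t-test on change scores. A change score subtracts the baseline with its slope fixed at 1. Whenever the true slope of the later score on the baseline differs from 1, regressing on the baseline leaves less residual variance. The planned test then gives up precision on the main efficacy comparison although the data needed to recover it are in hand.

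The second issue is the match between aim and analysis. A T1-to-T5 comparison shows whether the arms differ in total change at six months. It can be significant when gains have partly eroded since T4, and it cannot show whether either arm held what it had gained by T4. Maintenance in that sense has no contrast in the plan.

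**Working it through.** **Inputs from the article.** 80 per arm, d=0.43, alpha 0.05 one-tailed, stated power 0.85 (Power Estimation); entry rule ECBI Intensity of at least 132 (Eligibility); allocation 1:1, stratified by child gender (Recruitment Procedure). Power Estimation describes the pilot effect as a difference in change, so d is taken as standardised by the SD of change.

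**Assumed, not in the article.** Baseline ECBI before the entry cut: mean 150-160, SD 25. Pre-post correlation rho before the cut: 0.4-0.7.

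**1. The plan's own figure.** Noncentrality = 0.43 x sqrt(80/2) = 2.72, with 158 degrees of freedom. One-sided power is 0.856 (0.859 by the normal approximation), so the stated 0.85 reproduces. Two-sided it would be 0.771.

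**2. Variance ratio with the entry cut.** Let beta be the slope of the later score on baseline, Ve the residual variance and Vb the baseline variance after truncation. The change score has variance Ve + (1 - beta)^2 x Vb; the baseline-adjusted score has Ve. With equal SDs before truncation, beta = rho and Ve = 25^2 x (1 - rho^2). Truncating a normal distribution at 132 gives a baseline SD of 18.5 (mean 150) or 20.4 (mean 160).

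- Largest gain (rho 0.4, mean 160): Ve = 625 x 0.84 = 525.0; penalty = 0.36 x 415.7 = 149.6; ratio = 525.0/674.6 = 0.78.
- Smallest gain (rho 0.7, mean 150): Ve = 625 x 0.51 = 318.8; penalty = 0.09 x 342.3 = 30.8; ratio = 318.8/349.6 = 0.91.

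**3. Power.** Effective d = 0.43/sqrt(ratio).

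| Analysis | Ratio | Effective d | One-sided | Two-sided |
|---|---|---|---|---|
| Planned interaction | 1 | 0.43 | 0.86 | 0.77 |
| Adjusted, smallest gain | 0.91 | 0.45 | 0.88 | 0.81 |
| Adjusted, largest gain | 0.78 | 0.49 | 0.92 | 0.87 |

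**4. Effect of the cut.** Without truncation the ratio is (1 - rho^2)/(2(1 - rho)) = (1 + rho)/2, that is 0.70-0.85 for rho 0.4-0.7. At rho 0.5 it is 0.75, with power 0.93 one-sided and 0.88 two-sided. Selecting on baseline leaves the slope unchanged in this model and shrinks only Vb, so the entry rule reduces the gain from adjustment.

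**5. What T2 and T3 would add.** With T4 complete and an unstructured model, they add nothing to the T4 contrast. With a fraction m missing T4, the variance relative to using baseline alone is 1 - m x R2, where R2 is the share of T4 variance, given baseline, explained by T2 and T3. Under an assumed compound-symmetric correlation of 0.5-0.7, R2 is 0.167-0.24. For assumed m of 0.2-0.3 the relative variance runs from 1 - 0.2 x 0.167 = 0.967 to 1 - 0.3 x 0.24 = 0.928, a saving of about 3-7%.

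**6. Aim against contrast.** The two tests are T1 with T4, and T1 with T5. T4 with T5 is not among them.

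**The case against.** The planned test is sound. Under 1:1 randomisation a change-score comparison is unbiased, it already subtracts the baseline, and hypothesis, pilot effect size and test are all framed as change. All of that stands: the loss is efficiency only.

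Four stronger readings are tempting, and the article does not support them.

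- *The trial is underpowered at 0.77.* That figure is two-sided. Power Estimation specifies a one-tailed test, and on those terms the planned analysis meets 0.85. Sidedness is a separate question.
- *The entry cut-off makes the change score worse.* Step 4 shows the reverse.
- *T2 and T3 are discarded.* They are absent from the Hypothesis 2 tests only. The mediation model is described as using repeated measurements, and the article does not say whether these waves enter the multiple imputation, a detail that may properly sit in a fuller plan. Their contribution to the T4 contrast is slight in any case.
- *The maintenance aim has no test.* The pre-to-follow-up ANOVA tests the arm difference in change at six months, which covers the long-term part of aim 2. Only the direct T4-to-T5 comparison is missing.

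**Conclusion.** The point holds as lost efficiency plus one missing contrast; the analysis is not invalid. Adjusting for the baseline score would add roughly 3 to 7 points of one-sided power (0.86 to 0.88-0.92), or 4 to 9 points two-sided (0.77 to 0.81-0.87). The size rests on the assumed baseline mean, SD and pre-post correlation, and on reading d as standardised by the SD of change. The direction does not depend on the assumed values: adjustment has the smaller residual variance whenever the baseline slope differs from 1. The absence of a T4-to-T5 contrast follows from the text and needs no assumption.

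**What to change.** For each Hypothesis 2 outcome, replace the two ANOVAs with a pre-specified baseline-adjusted analysis, in one of two forms:

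- ANCOVA at T4 and at T5 on arm, baseline score and child gender (the stratification factor); or
- one longitudinal mixed model on T2-T5 with arm, visit, arm x visit, baseline score x visit and child gender, with pre-specified arm contrasts at T4 and at T5.

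In either case add a contrast for the T4-to-T5 change by arm, so that maintenance is addressed directly.

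No further data collection is needed, because every variable is already scheduled. The cost is small but real: the trial is preregistered and enrolment was under way (100 participants by the end of December 2024), so the change needs a documented amendment. The timeline in Table 1 starts analysis in January 2027, and the amendment should be in place before then.
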